## Abstract

**Background:**

Global elimination of schistosomiasis as a public health problem is set as target in the new World Health Organization’s Neglected Tropical Diseases Roadmap for 2030. Due to a long history of interventions, the Zanzibar islands of Tanzania have reached this goal since 2017. However, challenges occur on the last mile towards interruption of transmission. Our study will investigate new tools and strategies for breaking schistosomiasis transmission.

**Methods:**

The study is designed as an intervention study, documented through repeated cross-sectional surveys (2020–2024). The primary endpoint will be the sensitivity of a surveillance-response approach to detect and react to outbreaks of urogenital schistosomiasis over three years of implementation. The surveys and multi-disciplinary interventions will be implemented in 20 communities in the north of Pemba island. In low-prevalence areas, surveillance-response will consist of active, passive and reactive case detection, treatment of positive individuals, and focal snail control. In hotspot areas, mass drug administration, snail control and behaviour change interventions will be implemented. Parasitological cross-sectional surveys in 20 communities and their main primary schools will serve to adapt the intervention approach annually and to monitor the performance of the surveillance-response approach and impact of interventions. *Schistosoma haematobium* infections will be diagnosed using reagent strips and urine filtration microscopy, and by exploring novel point-of-care diagnostic tests.

**Discussion:**

Our study will shed light on the field applicability and performance of novel adaptive intervention strategies, and standard and new diagnostic tools for schistosomiasis elimination. The evidence and experiences generated by micro-mapping of *S. haematobium* infections at community level, micro-targeting of new adaptive intervention approaches, and application of novel diagnostic tools can guide future strategic plans for schistosomiasis elimination in Zanzibar and inform other countries aiming for interruption of transmission.

*Trial registration* ISRCTN, ISCRCTN91431493. Registered 11 February 2020, https://www.isrctn.com/ISRCTN91431493

## Background

Schistosomiasis is a neglected tropical disease (NTD) with a considerable impact on global health [1, 2]. Since the mid-1980s, efforts in endemic countries mainly focused on the control of morbidity using preventive chemotherapy with praziquantel [3]. A paradigm shift occurred in recent years: in 2012, the World Health Organization (WHO) declared as goal to eliminate schistosomiasis as a public health problem and to interrupt transmission in selected areas by 2025 [4]. In the new WHO Roadmap on NTDs published in 2021, the global elimination of schistosomiasis as a public health problem and the validated absence of infections in humans in 25 among 78 endemic countries are set as targets for 2030 [5].

There are several countries and areas that have made great progress in the fight against schistosomiasis in the past and may aim to achieve full interruption of transmission in the next few years [6–10]. These countries will need clear guidance on which intervention strategies to apply, which population groups to target, which diagnostics to use, and at what thresholds to change and adapt their strategies [11–13]. Moving from morbidity control towards elimination as public health problem and interruption of transmission, WHO recommends in their schistosomiasis progress report 2001–2011 and strategic plan 2012–2020, the intensification of mass drug administration (MDA) and the implementation of complementary public-health interventions in addition to preventive chemotherapy (Fig. 1) [4]. In World Health Assembly resolution 65.21 (05/12) these complementary interventions are indicated as “strengthened health systems, […] provision of water and sanitation, as well as hygiene education and snail control” [14]. In the new WHO NTD Roadmap 2021–2030, besides MDA, the following core strategic interventions against schistosomiasis are listed: Water, Sanitation and Hygiene (WASH), vector control, veterinary public health, case management and other interventions such as behaviour change, self-care and environmental management [5]. Finally, according to WHO, once interruption of transmission is close or has been achieved, affected countries will need to implement a surveillance system “to detect and respond to resurgence of transmission and to prevent reintroduction from regions where the disease is still endemic” [4]. Despite these recommendations, specific guidance and thresholds on when, where and how to adapt intervention strategies in near-to-elimination settings is yet to be developed [11, 12, 15]. More evidence on the feasibility, impact, effectiveness and sustainability of multi-pronged intervention approaches needs to be generated.

**Fig. 1 Fig1:**

Programmatic steps to control and eliminate schistosomiasis. In green and gray text boxes: recommendations according to WHO [4]; in blue fonts and yellow text box: additional components of the SchistoBreak study. PC: preventive chemotherapy; IU: implementation unit

A wealth of experience and insights regarding multi-disciplinary interventions and research for urogenital schistosomiasis elimination was gained over the past decade from 2011 to 2020 within the Zanzibar Elimination of Schistosomiasis Transmission (ZEST) project [6, 16–19]. The islands Pemba and Unguja, belonging to the Zanzibar archipelago of the United Republic of Tanzania, used to be highly endemic for urogenital schistosomiasis in the past century [20–22]. To combat urogenital schistosomiasis, caused by *Schistosoma haematobium*, on the islands, regular MDA campaigns with praziquantel administration to schoolchildren and the whole community were implemented since the 1980s [23–26]. In 2010, Zanzibar had managed to reach low prevalences of *S. haematobium* infections and subsequently committed to eliminate urogenital schistosomiasis from the islands [17, 18]. From 2012 till 2017, in addition to biannual MDA, some randomised areas received interventions with chemical mollusciciding to target *Bulinus globosus,* the intermediate host snail for *S. haematobium* in Zanzibar [27, 28] and behaviour change measures to reduce people`s freshwater contact [17, 19]. In 2017, most areas on the Zanzibar islands had eliminated urogenital schistosomiasis as a public health problem (defined as < 1% heavy intensity infections) [5, 17, 18]. However, transmission of *S. haematobium* infections was not yet interrupted and several challenges were identified on the way towards schistosomiasis elimination.

These challenges included a marked temporal and spatial heterogeneity of *S. haematobium* prevalence across the islands, as well as the application of standard diagnostic tests with insufficient sensitivity to detect light intensity infections [6, 17, 18, 29–32]. While most of the study sites showed continuously low prevalences from 2011/12 to 2020, some “hotspot” areas with consistent or recurring moderate or high prevalences existed [6, 17, 18]. To address this heterogeneity and to sustain and accelerate the gains made towards elimination, there is a need to target and regularly adapt interventions to the local micro-epidemiology [12, 17, 18].

In low-prevalence areas, it will be important to progress towards complete interruption of transmission by applying an intervention approach that enables the reliable identification and treatment of all cases and thus prevents outbreaks and recrudescence, without overtreating a mostly healthy population [18] and thereby risking treatment fatigue and/or the development of resistance against praziquantel [33]. The participation of countries in the development and use of surveillance-response approaches to ensure that the progress made is sustained and advanced has been stressed in several publications [15, 34–39].

In hotspot areas that are often characterized by a large number of water bodies containing the intermediate host snails and proximity of households and schools to transmission sites [40, 41] there is a need to tackle the persistent transmission to progress towards elimination using a comprehensive package of interventions, including MDA, but also other interventions such as snail control and behaviour change communication and WASH measures [11, 17, 18, 32].

Accurate, reliable and affordable diagnostic tools are an essential requirement for NTD programmes and have been identified as a priority area for critical action in the WHO NTD Roadmap 2021–2030 [5, 13, 15, 42, 43]. Moving towards schistosomiasis elimination, there is an enhanced need for sensitive and specific diagnostic tests that are high-throughput, and affordable and applicable at the point of care to assess reliably *S. haematobium* infections, prevalences and incidence [13, 43]. An accurate picture of the endemic situation is important for programmatic decision making, to tailor specific intervention packages in line with (yet to be developed) target thresholds to those in need, to determine correctly the performance and impact of interventions in elimination settings, and to document sustained elimination [13, 29–31, 44].

In our protocol, we describe an implementation research study that will address the focality and heterogeneity of *S. haematobium* transmission, using novel adaptive intervention strategies as well as standard and new diagnostic tools for schistosomiasis elimination in Zanzibar.

## Methods/design

### Study aim

The overall objective of the study is to investigate new tools and strategies for breaking schistosomiasis transmission.

### Primary and secondary objectives

The primary objective of this study is to quantify the sensitivity of an adaptive surveillance-response approach for its ability to detect *S. haematobium* infected individuals in low-prevalence areas to trigger an appropriate intervention response. The primary outcome variable will be the number of *S. haematobium* infected individuals detected and reported through the surveillance approach divided by the number of positive individuals in the population as extrapolated from the cross-sectional surveys, i.e. the mean sensitivity of the surveillance-response approach determined over 3 years.

Secondary outcome analyses will cover additional performance parameters of the surveillance approach, as defined by WHO [45]. Moreover, we will assess the impact of multi-disciplinary interventions in hotspot areas, as well as the coverage of test-and-treat activities in low-prevalence areas and of MDA in hotspot areas. Other secondary outcomes will include the accuracy of several diagnostic approaches and micro-mapping of characteristics of the study shehias, including the number and location of schools, madrassas (Islamic schools), and health facilities, the number and location of water bodies and the abundance of intermediate host snails of the genus *Bulinus*.

### Study design

The study is designed as intervention study, documented through repeated cross-sectional surveys to assess the performance of the surveillance-response approach.

### Study setting

The implementation research study with the acronym “SchistoBreak” is a joint project with partners from the Swiss Tropical and Public Health Institute (Swiss TPH), Basel, Switzerland the Public Health Laboratory-Ivo de Carneri (PHL-IdC), Pemba, United Republic of Tanzania and the Neglected Diseases Programme of the Ministry of Health, Social Welfare, Elderly, Gender, and Children (MoHSWEGC) Zanzibar, United Republic of Tanzania. The fieldwork for the SchistoBreak study will be conducted in Pemba, an island that forms part of the Zanzibar archipelago, from March 2020 to June 2024. The population density of Pemba was 530 people/km^2^ in 2012 and the projected population for 2019 was around 500,000 people [46]. The study area will consist of 20 shehias (small administrative areas) located in the rural districts Micheweni and Wete in the north of Pemba (Fig. 2). The average population size in the study shehias is ~ 3,900 individuals per shehia [47]. To address the small-scale heterogeneity in the study area and to micro-target implementation, not the districts but each shehia will serve as one implementation unit (IU). The 20 study shehias were selected based on their isolated but contiguous location in the north of Pemba and very good documentation of *S. haematobium* prevalences in 10 among the 20 shehias from 2012 to 2020 [6, 17, 18].

**Fig. 2 Fig2:**
[figure not shown]
Twenty study shehias (implementation unit) of the SchistoBreak project in Wete and Micheweni districts in Pemba, Tanzania. The image base map (United Republic of Tanzania – Subnational administrative boundaries) was downloaded from OCHA services (https://data.humdata.org/dataset/tanzania-administrative-boundaries-level-1-to-3-regions-districts-and-wards-with-2012-population). The data source is: Tanzania National Bureau of Statistics/UN OCHA ROSA. The data are published under the following license: Creative Commons Attribution for Intergovernmental Organisations (CC BY-IGO; (https://creativecommons.org/licenses/by/3.0/igo/legalcode)). Additionally, we received written permission to use and adapt the data from the UN Office for the Coordination of Humanitarian Affairs (OCHA). Additional shape files for the map (shehia boundaries) were provided by the Zanzibar Commission of Lands to the Zanzibar Neglected Diseases Programme

The study will take place in communities, schools and health facilities. In Zanzibar, public primary schools contain the grades 1–6 and some schools include a nursery school. In addition, most of the children in Zanzibar visit a madrassa [48]. The net enrolment rate in primary schools was 68.4% in Micheweni and 81.9% in Wete in 2014/15 [49].

### Participant eligibility

All individuals who meet the following inclusion criteria are eligible to participate in the study:All persons aged ≥ 4 years, living in the study shehias.Submitted informed consent form (ICF) signed by parent or legal guardian in case of participating children and adolescents, or signed by the participant in case of participating adults, and submitted assent form in case of children aged 12 years and older signed by the participating children.Urine sample with sufficient volume to perform diagnostic tests provided.

All individuals who do not meet the following exclusion criteria are not eligible to participate in the study:Children < 4 years.Children, adolescents and adults not living in the study area.ICF not submitted or not signed by parent or legal guardian in case of participating children or adolescents or not signed by the participant in case of participating adults. Assent form not submitted or not signed by the child in case of participating children aged 12 years or older.No urine sample of sufficient volume to perform diagnostic tests provided.

### Shehia characteristics survey

Upon start of the SchistoBreak project, we will conduct a survey to gain an aggregate picture of the characteristics of the 20 study shehias. In a first step, in each shehia, we will meet with the sheha (head of shehia) and invite him to participate in a questionnaire interview to collect data about the population size, the number and type of schools, natural open freshwater bodies, health facilities and public clean water sources available in each shehia. Subsequently, with the sheha’s permission and the support of an assistant sheha, we will visit all nursery, primary and secondary schools and all madrassas in the shehia and assess the geolocation, type of school, and the number of children enrolled in the school. Moreover, we will visit all known human water contact sites (HWCSs) at the natural open freshwater bodies in the shehias and collect data of locality, type and characteristics of the water body, regular behavioural activities at the water bodies and the abundance of freshwater snail species and specifically the intermediate host snail *Bulinus*. Finally, we will visit all health facilities in the shehias and determine the location and type of facility, i. e. whether they are of public or private status and offer mother and child health care services. For all processes of data collection during the shehia characteristics survey, we will use Open Data Kit (ODK) software (www.opendatakit.org), installed on a computer tablet (Samsung Galaxy Tab A 2019).

### Annual cross-sectional parasitological surveys

The annual cross-sectional surveys will be implemented in all 20 communities and their main public primary schools at sub-district shehia level. This micro-mapping approach will allow us to determine *S. haematobium* prevalences in the school-aged population, which is at highest risk of schistosomiasis, as well as in the whole community to get an accurate picture of infection levels in preschool-aged children, school-aged children, adolescents and adults. The cross-sectional surveys will serve to stratify the study area into low-prevalence and hotspot IUs and hence to micro-target the interventions according to pre-set prevalence thresholds. Moreover, the cross-sectional surveys will allow to determine and monitor the performance of the surveillance-response approach and impact of interventions over the study period. Participants of the annual cross-sectional parasitological surveys identified as infected with *S. haematobium* will be offered treatment with praziquantel (40 mg/kg using a dose pole) [50].

### Annual community-based parasitological surveys

#### Selection of houses and participants

For the annual community-based surveys, 70 housing structures per shehia will be selected by a computer-based randomisation procedure from Geographical Information System (GIS) shape files provided by the Zanzibar Mapping Initiative (http://www.zanzibarmapping.com) of the Commission of Lands Zanzibar. Randomly selected housing structures will be located by field enumerators by using the navigation app Maps.me (https://www.maps.me/) combined with ODK installed on a computer tablet (Samsung Galaxy Tab A 2019). Accounting for a 30% dropout of housing structures that may not be inhabited (i.e. shops, sheds, mosques, houses under construction or abandoned houses) and households without any member willing to participate, we estimate that we will have a final sample size of 50 houses per shehia included in the survey. People sharing the same kitchen or pot will define a household. All household members meeting the inclusion criteria will be invited to participate in the survey and to provide one own urine sample, which will be examined for *S. haematobium* infection markers. With an average of five people per household, we estimate to collect urine samples from a total of 250 participants per shehia. Additionally, one adult household member present at the first visit to the house will be invited to participate in a questionnaire survey to assess household characteristics. If more than one adult is present and eligible to participate at first visit, we will randomly select the participant of the questionnaire survey by using a playing-cards approach.

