### School-based parasitological surveys

#### Selection of participants

The annual school-based cross sectional survey will be conducted in the main public primary school of each shehia. If a shehia has several public primary schools, the school with most students will be surveyed. If a shehia has no public primary school, no school will be surveyed. In each of the schools, a total of 175 students aged 4–17 years will be randomly selected for urine collection. For this purpose, one class of each nursery and standard 1–6 grades, will be selected based on computer-randomised lists. In the selected classes, all children will line up, stratified by sex. Subsequently, we will systematically select each third child in the lines to be included in the study until 25 children per class are reached. This procedure will be continued until we reach a total of 175 selected children from the 7 selected grades. Accounting for a 20% drop-out due to non-consenting parents, absenteeism of children or inability to produce a urine sample of sufficient volume, we aim for a final sample size of 20 children per standard (i.e. a total of 140 students per school).

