### Sample size

We run a series of simulations to assess how precisely the sensitivity of the surveillance system can be estimated. We modelled different scenarios with varying prevalences in schoolchildren as well as in the general population, different values for clustering and different assumptions for diagnostic test accuracy and surveillance system performance. The results revealed that sampling an average of 140 schoolchildren and 250 community members in each of 15 low-prevalence shehias in the cross-sectional surveys enables us to estimate the prevalence with a median precision (defined as one half length of the confidence interval) of 10 to 15 percentage-points in schoolchildren and of 5 to 7 percentage-points in the general population. The bias (defined as difference between the sensitivity calculated using the apparent prevalence observed during cross-sectional surveys and the sensitivity calculated using the "true" apparent prevalence observed during the surveillance activities) had a median of zero and an interquartile range from − 0.05 to 0.05.

Hence, conducting the cross-sectional surveys in the schools and communities of all 20 study shehias, the yearly total sample is 7800 individuals (ca. 10% of the population, based on an average of 4000 inhabitants per shehia).

In addition, during the surveillance activities in 15 low-prevalence shehias, we roughly estimate to test annually about 12,150 individuals (ca. 20% of the population). Among them, around 7500 will be subjected to active surveillance in high-risk schools (estimated n = 15 shehias*1 school*450 children + estimated n = 15 shehias*1 school*50 children = 7500 samples per year), 750 to reactive surveillance in households (estimated n = 15 shehias*10 households*5 inhabitants = 750 samples per year) and 1500 at mobile test-and-treat stalls (estimated n = 15 shehias*10 water bodies *10 people = 1500 per year), and 2400 to passive surveillance in health facilities (estimated n = 20 health facilities*12 months*10 patients = 2400 samples per year).

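### The planned 250 community participants per shehia, and the 7,800 a year built on them, leave out individual-level losses, so the stated precision rests on near-maximum sizes

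*Protocol article*

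**What the plan says.** The community survey starts from structures: "70 housing structures per shehia will be selected by a computer-based randomisation procedure". One loss is then applied: "Accounting for a 30% dropout of housing structures that may not be inhabited", extended to "households without any member willing to participate". This leaves 50 houses per shehia, and the article concludes: "With an average of five people per household, we estimate to collect urine samples from a total of 250 participants per shehia".

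Participant eligibility is narrower than residence. It requires "All persons aged ≥ 4 years, living in the study shehias", signed consent (and assent from age 12), and a urine sample of sufficient volume.

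The school survey selects 25 children in each of seven grades (nursery and standards 1-6), 175 in all. It takes off 20% for non-consent, absence and insufficient urine, which gives 140. It also states: "If a shehia has no public primary school, no school will be surveyed". Study setting describes public primary schools as grades 1-6 and adds that "some schools include a nursery school".

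Sample size uses averages of 140 schoolchildren and 250 community members in each of 15 low-prevalence shehias. From these it reports a median half-width of 10 to 15 percentage points in schoolchildren and 5 to 7 in the general population. It then applies the same sizes to all 20 shehias: "the yearly total sample is 7800 individuals".

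**The concern.** The 30% covers only houses that yield nobody. A house with one willing member counts as retained and is credited with five urine samples. The five are residents: the reactive-surveillance estimate in Sample size uses the same multiplier and calls them inhabitants. Some residents will be under 4, absent, unwilling or unable to give enough urine. The authors allow for such losses in schools but not in homes.

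The yearly total has a similar weakness. It counts a surveyed school yielding 140 in every shehia, while the selection rules provide for shehias that have no school to survey.

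The community and school surveys supply the prevalences from which the number of infected people is extrapolated, and that number is the denominator of the primary outcome. If the expected sizes are too high, the stated precision is too favourable.

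**Working it through.** **1. The plan's own figures**

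- Houses: 70 × (1 − 0.30) = 49, stated as 50.
- Community: 50 × 5 = 250 (49 × 5 = 245).
- School: 7 × 25 = 175; 175 × (1 − 0.20) = 140.
- Total: 20 × (250 + 140) = 7,800.

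All of these reproduce, and 49 against 50 is trivial rounding.

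**2. What 250 requires**

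Expected community yield = houses × 5 × (share aged 4 or over) × (individual response among those eligible). The plan's 250 follows only if both shares equal 1, with one household of five per house.

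**3. Yield with individual losses**

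The document gives neither share, so both are assumptions.

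| Houses | Aged ≥ 4 | Response | Yield per shehia |
|---|---|---|---|
| 50 | 90% | 80% | 250 × 0.72 = 180 |
| 49 | 90% | 80% | 245 × 0.72 = 176 |
| 49 | 85% | 70% | 245 × 0.595 = 146 |
| 49 | 90% | 90% | 245 × 0.81 = 198 |

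With 180 per shehia and 140 in all 20 schools, the total is 20 × (180 + 140) = 6,400.

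**4. School side of the total**

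- Each shehia without a public primary school removes 140. With 18 surveyed schools and 250 per community, the total is 20 × 250 + 18 × 140 = 7,520.
- A school without a nursery has six grades. At 25 per class, 6 × 25 × 0.8 = 120 if nothing is substituted.
- The article does not say how many shehias or schools fall in either group, so these are conditional figures.

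**5. Effect on precision**

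The simulation cannot be repeated from the article, because its prevalences, clustering values and test accuracies are not given. Two approximations bracket the effect.

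- Independent people: the half-width scales as √(250/n). For n = 198 this is 1.12, and for n = 146 it is 1.31, so 12% to 31% wider.
- Clustering by shehia: variance is proportional to [1 + (n − 1) × ICC]/n, with an assumed ICC of 0.01 to 0.05.

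| n | ICC 0.01 | ICC 0.05 |
|---|---|---|
| 250 | 3.49/250 = 0.01396 | 13.45/250 = 0.05380 |
| 198 | 2.97/198 = 0.01500 | 10.85/198 = 0.05480 |
| 146 | 2.45/146 = 0.01678 | 8.25/146 = 0.05651 |

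The square roots of the variance ratios against n = 250 give a widening of about 4% (ICC 0.01) or 1% (ICC 0.05) at n = 198, and about 10% or 2.5% at n = 146.

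**The case against.** The strongest reply is that nothing is miscalculated: every multiplication reproduces, and the article presents 250 as an estimate. That stands as far as it goes. The difficulty is in what the multiplication leaves out, and the article's own eligibility rules show the omission. No unseen document is needed to see it.

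Second, structures are sampled, while a household is defined by a shared kitchen or pot, so one structure may hold several households. This could offset part of the loss, and it is why 250 is near a maximum and not a strict ceiling. To restore 250 at 90% and 80%, however, each house would need 5/0.72 = 6.9 residents, about 1.4 households of five. The article does not rely on this; it multiplies 50 houses by one household each.

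Third, the team revisits the next day and spends three days in each shehia. That should raise response, but it cannot make children under 4 eligible.

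Fourth, schools. A reader might infer that 140 should simply read 120. The documents do not support that as a flat claim: the number of surveyed schools without a nursery is not given, and selection is said to continue until 175 are reached. Equally, no substitution rule is stated for a school with six grades, and the 175 are to come from seven. Likewise, the rule for shehias without a public primary school does not show that any exist.

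Fifth, the consequence is limited. The primary outcome is estimated, not tested, and the Discussion already concedes that the study is underpowered for changes in prevalence.

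**Conclusion.** The point holds for the community figure. As derived, 250 per shehia is close to a maximum, and the simulation treats it as an average. A plausible expectation is about 180, with a range of about 146-198, under assumed shares of 85-90% aged 4 or over and 70-90% individual response. The total of 7,800 inherits this. It also depends, to an extent the article does not state, on every shehia having a surveyed school that yields 140.

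Two stronger readings should be resisted:

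- A reader might infer that community intervals will be 12-31% wider. That treats participants as independent and is an upper approximation. The simulations varied clustering and the analysis allows for it. Under the assumed ICCs the widening is roughly 1-10%, and clustering within households would also make the loss of members inside houses cost less than square-root scaling suggests.
- A reader might infer that smaller samples move the hotspot cut-offs. They do not: the threshold is a proportion of the realised sample, and a different whole number of positives is only rounding.

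The direction is therefore clear and the size probably modest. The stated sizes and precision should still be corrected, since the described sampling does not deliver them as averages.

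**What to change.** 1. Restate the expected community sample per shehia as 49-50 houses × 5 × (share aged 4 or over) × (individual response), giving both shares and their source. Use realised survey numbers where they exist. If several households per structure are expected, state that number too.
2. Restate the school total from the actual number of shehias with a public primary school and the nursery status of each surveyed school. Say what happens to the target of 175 when there are only six grades. The shehia characteristics survey already collects the number and type of schools.
3. Re-run the existing clustered simulation at those sizes, and replace 250, 7,800 and the precision figures with the results. Take the widening from that re-run and not from square-root scaling.

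The cost is a few restated figures and one simulation run. No extra enrolment or design change is needed. The only downside is slightly less favourable stated precision.
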